**Methods:**

In total, 334 participants aged 3–18 years attending epilepsy services will be screened for mental health disorders with the Strengths and Difficulties Questionnaire (SDQ) and the diagnostic Development and Wellbeing Assessment (DAWBA). Those identified as having a mental health disorder and consenting to the trial will be randomised to either receive up to 22 sessions of the modular psychological intervention (MATCH-ADTC) delivered over the telephone over 6 months by non-mental health professionals in addition to usual care or to assessment-enhanced usual care alone. Outcomes will be measured at baseline, 6 months and 12 months post-randomisation. It is hypothesised that MATCH-ADTC plus usual care will be superior to assessment-enhanced usual care in improving emotional and behavioural symptoms. The primary outcome is the SDQ reported by parents at 6 months. Secondary outcomes include parent-reported mental health measures such as the Revised Children’s Anxiety and Depression Scale, quality of life measures such as the Paediatric Quality of Life Inventory and physical health measures such as the Hague Seizure Severity Scale. Outcome assessors will be blinded to group assignment. Qualitative process evaluations and a health economic evaluation will also be completed.

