MATCH-ADTC involves a weekly phone/online video call with the therapist who carries out the initial face-to-face assessment; parents complete measures at home and email them to the therapist before each session, and strategies are practiced at home. Face-to-face therapy sessions are permitted if clinically indicated or strongly preferred by the family. MATCH-ADTC comprises an average of 16 sessions but there is flexibility as many young people will have multiple mental health disorders whereas others may have one. MATCH-ADTC uses an algorithm to tailor the treatment to each young person’s individual needs and participants with co-occurring mental health disorders can have each of those addressed within the intervention. Those with intellectual disabilities may need to go at a slower pace than others and therefore may require more sessions. The minimum number is expected to be 10 and the maximum number of sessions is 22. The intervention must be completed within a 6-month window. The two booster sessions may be completed outside of this window. Some patients may receive fewer than 10 sessions providing that there is mutual agreement that their goals have been reached. All therapy sessions will be delivered within 6 months of randomisation although booster sessions can occur between 6 and 12 months post-randomisation. Clinical sessions including face-to-face sessions and telephone/online video calls will be audio and/or video recorded to ensure the sessions are delivered consistently. Key content of MATCH-ADTC for depression includes cognitive and problem-solving strategies and scheduling pleasurable activities; anxiety is addressed using exposure techniques; behavioural strategies, delivered through the parents, include one-on-one time, praise, effective instruction-giving, rewards and ignoring unwanted behaviour; trauma is addressed through developing a trauma narrative, exposure and safety planning. Session by session measurement of symptoms and progress towards self-identified goals is also included as part of the intervention.

Children and young people in the MATCH-ADTC arm will also access usual care for the mental health disorder if required as per Fig. 1.

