#### Secondary outcomes

Revised Child Anxiety and Depression Scale (RCADS) [34]. This 47-item questionnaire is one of the main outcome measures used in the Children and Young People’s Improving Access to Psychological Therapies (CYP-IAPT) Programme. It is included to allow comparison with this national initiative and has parent and child versions, the subscales are reliable (Cronbach *α* .78–.88) and the measure has discriminant, convergent and factorial validity in a clinical sample [35]. For the trial, the parent version will be used for data completeness.Patient Health Questionnaire (PHQ-9) [36]. This is a 9-item measure of depression in adults completed by the parent/carer about their own mental health.Generalised Anxiety Disorder Assessment (GAD-7) [37]. This is a 7-item measure of generalised anxiety disorder, completed by the parent/carer about their own mental health.Hague Seizure Severity Scale (HASS) [38]—this is a parent-report questionnaire which rates carers’ subjective experiences of the severity of their child’s seizures. Items are statements, which are rated on a 4-point scale from most to least severe (e.g. ‘always’, ‘usually’, ‘sometimes’ or ‘never’). Items describe the length, type and outcomes of a seizure—for example ‘how long do the jerks or cramps last during an attack?’Paediatric Quality of Life Epilepsy Module (PedsQL) [39]. The PedsQL measures the impact of epilepsy on quality of life.Number of serious adverse events. Serious adverse events are those that result in death, are life threatening, require hospitalisation or prolong existing hospitalisation, result in persistent or significant disability or incapacity, or result in a congenital anomaly or birth defect or another important medical condition.

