### Adverse event reporting and harms {22}

For the purposes of the MICE trial, only serious adverse events will be reported. All serious adverse events (SAEs) occurring during the trial observed by the investigator or reported by the participant, whether or not attributed to the trial treatment will be recorded on the database. Low-grade adverse events that do not meet the seriousness criteria will not be reported, for example a grade 1 or 2 epileptic seizure that does not result in hospitalisation.

Investigators should notify CCTU immediately and within 24 h at the latest of any SAEs occurring from the time of randomisation until 30 days after the participant completes trial treatment. From this point forward, the site will notify the CCTU of SAEs that are considered related to the trial intervention if they become aware of them until end of follow-up.

Participants must be followed up until clinical recovery is complete, or until the event has stabilised. Follow-up should continue after completion of trial treatment and/or trial follow-up if necessary. Follow-up SAE forms (clearly marked as follow-up) should be completed and emailed to CCTU as further information becomes available. Additional information and/or copies of test results, etc., may be provided separately.

Medically qualified staff appointed by the sponsor will review all SAE reports received. The reviewer will complete the assessment of expectedness.

SAEs that are considered to be related to the trial (resulted from administration of any of the research procedures) and unexpected must be reported to the REC and DMEC. If the related and unexpected event is fatal or life threatening, it must be reported within 7 days of becoming aware of the event; other related and unexpected events must be reported within 15 days.

A list of expected occurrences as a result of the trial treatment is as follows:

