Significant deterioration in behaviour operationalised as consistent decline for three consecutive weeks, over four measurement time points, of at least 5 points for relevant behaviour based goals (e.g. as a result of an ‘extinction burst’)Significant deterioration in anxiety operationalised as consistent decline for three consecutive weeks, over four measurement time points, of at least 5 points for relevant anxiety-based goals (e.g. as a result of exposure to feared situations)Significant deterioration in mood operationalised as consistent decline for three consecutive weeks, over four measurement time points, of at least 5 points for relevant mood-based goals (e.g. as a result of cognitive challenging)

Where the SAE falls outside of this list, it must be deemed to be unexpected by the clinical reviewer.

CCTU will keep investigators informed of any safety issues that arise during the course of the trial.

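### Deteriorations the protocol expects from treatment are defined on goal ratings described only for the MATCH-ADTC arm and are not in themselves SAEs, so they are neither captured nor compared as harms

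*Protocol article*

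**What the plan says.** All references are to the protocol article.

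- **What is reported.** Adverse event reporting and harms {22}: "For the purposes of the MICE trial, only serious adverse events will be reported". The same section adds: "Low-grade adverse events that do not meet the seriousness criteria will not be reported".
- **What counts as serious.** Secondary outcomes, under Outcomes {12}: "Serious adverse events are those that result in death, are life threatening, require hospitalisation or prolong existing hospitalisation". The definition goes on to disability, congenital anomaly and an open category for other important medical conditions.
- **What treatment is expected to cause.** Section {22} introduces the list with "A list of expected occurrences as a result of the trial treatment is as follows". It has three items: deterioration in behaviour, in anxiety and in mood. The behaviour item requires a "consistent decline for three consecutive weeks, over four measurement time points, of at least 5 points for relevant behaviour based goals". The other two apply the same rule to anxiety-based and mood-based goals. Each item is linked to a treatment mechanism: an extinction burst, exposure, or cognitive challenging.
- **How the list is used.** "Where the SAE falls outside of this list, it must be deemed to be unexpected by the clinical reviewer". SAEs that are both related and unexpected must be reported to the ethics committee and the DMEC, within 7 days if fatal or life threatening and within 15 days otherwise.
- **Who has goal ratings.** MATCH-ADTC in addition to usual care: "Session by session measurement of symptoms and progress towards self-identified goals is also included as part of the intervention". The outcome schedule for both arms is in the Abstract: "Outcomes will be measured at baseline, 6 months and 12 months post-randomisation". No goal measure appears among the primary, secondary or health economic outcomes.
- **What is compared between arms.** Statistical methods {20a} compares parent SDQ total difficulties at 6 months (primary), the secondary outcomes (parent RCADS among them) separately at 6 and 12 months, and the proportion of children with any SAE by Fisher's exact test.

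**The concern.** The protocol names three ways in which treatment may make a child worse, defines them precisely and attributes them to the therapy. It then gives them no route into the harms results. An episode that meets the definition without also being serious is not reported as an adverse event, and the definition can be met only by a child who has session-by-session goal ratings. Some deterioration will also occur under usual care, so a count from therapy records alone could not be interpreted.

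At stake is the safety conclusion, not the primary analysis. The harms comparison rests on SAEs. The symptom comparisons are of means, and a null or favourable mean difference is compatible with a minority of children getting worse.

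There is a second consequence. The list is the only standard for expectedness. An SAE that coincides with a listed decline counts as expected and so falls outside the 7- or 15-day route to the ethics committee and the DMEC.

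**Working it through.** **Step 1. Set the sections side by side.**

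| Question | Listed deteriorations | Source |
|---|---|---|
| Measured how? | Goal ratings, four measurements over three weeks | {22} |
| Measured in MATCH-ADTC arm? | Yes, session by session | MATCH-ADTC in addition to usual care |
| Measured in usual-care arm? | Not described; shared outcomes are at baseline, 6 and 12 months | Abstract; Outcomes {12} |
| Serious in themselves? | No named criterion met; the open category leaves discretion | Secondary outcomes |
| Reported if not serious? | No | {22} |
| Compared between arms as a harm? | No; only any SAE is | {20a} |

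The list therefore has an effect only when an event is serious and also coincides with a listed decline. The effect is to class that event as expected.

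**Step 2. Number available for a by-arm comparison.** The plan's own sample size reproduces with rounding up at each step:
- Effect size 0.3, two-sided 5%, 80% power: 175 per arm.
- Baseline correlation 0.5: 175 × (1 − 0.5²) = 131.25, rounded up to 132.
- 14 children per therapist, ICC 0.01: 132 × (1 + 13 × 0.01) = 149.2, rounded up to 150.
- 10% loss: 150 / 0.9 = 166.7, rounded up to 167 per arm, or 334 in total, as stated.

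About 150 per arm would be analysed (334 × 0.9 / 2 = 150.3).

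**Step 3. An illustrative SDQ margin.** Reliable-change margin = 1.96 × √(2 × (1 − r)) baseline SDs. Primary outcome, under Outcomes {12}, gives two candidates for r:
- mean Cronbach alpha 0.73: 1.96 × √0.54 = 1.44 SD
- mean 4–6 month retest stability 0.62: 1.96 × √0.76 = 1.71 SD

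**Step 4. Precision of the difference in proportions.** Half-width = 1.96 × √(2 × p × (1 − p) / 150). The protocol gives no deterioration rate, so p is assumed:

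| Assumed rate in each arm | Half-width |
|---|---|
| 5% | 1.96 × √(2 × 0.05 × 0.95 / 150) = 4.9 points |
| 10% | 1.96 × √(2 × 0.10 × 0.90 / 150) = 6.8 points |
| 20% | 1.96 × √(2 × 0.20 × 0.80 / 150) = 9.1 points |

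**Step 5. Which rate is plausible for the 1.44 SD margin?** Assume normal scores, equal SDs and the plan's correlation of 0.5. The SD of change is then √(2 × (1 − 0.5)) = 1 baseline SD. The chance of worsening by more than 1.44 SD is about 7.5% with no mean change and about 4% with a mean improvement of 0.3 SD. The 5% and 10% rows are therefore the more relevant ones.

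**The case against.** **Symptoms are compared between arms.** A reader might infer that deterioration is never compared, or that the trial could report a clean safety result however many MATCH-ADTC children got worse. The protocol does not support either reading. Mean parent SDQ and RCADS are compared at 6 and 12 months with two-sided tests, and widespread worsening under treatment would move the primary outcome against it. What is not stated is any comparison of the proportion who worsen.

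**The SAE definition is not closed.** Its open category leaves room for clinical judgement, so it would be wrong to say a listed episode can never become an SAE. Nothing in the protocol, however, says these declines fall in that category.

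**An expectedness list need not apply to controls.** It concerns effects of a treatment that controls do not receive, and the Fisher comparison of any SAE does not use it. A short list also makes more events unexpected, which errs towards caution. This is right: that the list cannot be applied to a control child is not in itself a fault. The problem is that nothing else records or compares the harms it names.

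**The exemption is limited.** A serious event matching the list is still recorded, notified to the trials unit and counted in the SAE comparison, and the DMEC receives regular reports. Only the related-and-unexpected reporting is lost.

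**The SAP may add a deterioration table.** It is not shown and could do so. It could not undo the SAE-only rule or the list, both fixed in the protocol, nor supply goal ratings for the usual-care arm.

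**The remedy is partial and its figures are soft.** An extinction burst that resolves before 6 months would be missed. The reliability figures come from cited work and are applied here to a sample selected for high SDQ scores. A half-width of about 7 points would not reliably reveal a small harmed subgroup. All of this stands.

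**Conclusion.** The point holds as a fault in how harms are defined and reported. The expected deteriorations can be observed only in the MATCH-ADTC arm as described, are not SAEs in themselves, and go unreported as harms unless they are also serious. Between-arm evidence on worsening is limited to mean scores at 6 and 12 months and the proportion with any SAE, so a minority who deteriorate could be masked. The expectedness list does little beyond exempting a coinciding serious event from related-and-unexpected reporting.

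The primary analysis and the sample size of 334 are unaffected. A comparison of proportions would carry a half-width of about 5 to 9 percentage points. That rests on about 150 analysed per arm and on assumed rates of 5% to 20%, which have no source in the protocol. The 1.44 and 1.71 SD margins are examples. The change is a worthwhile low-cost improvement.

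**What to change.** 1. Add a harm outcome that both arms can meet: the number and proportion of children whose parent SDQ total, and separately RCADS total, has worsened from baseline at 6 and at 12 months beyond a margin fixed in advance. For the SDQ a reliable-change margin would serve, with the choice of reliability figure stated. For the RCADS the article quotes reliability for subscales only, so the margin for the total needs its own justification.
2. Report it by arm with a 95% CI for the difference, and supply it to the DMEC. The DMEC considers data in accordance with the SAP, so the table should be specified there too.
3. Reconcile the list in {22} with the seriousness criteria in Secondary outcomes. State whether the goal-rating declines are non-serious monitoring events in the MATCH-ADTC arm or part of the SAE expectedness standard, and how listed episodes that are not serious are recorded.

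The cost is protocol and SAP wording plus one descriptive table from data already collected in both arms. The limits are modest precision and no view of episodes that resolve before 6 months.

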### Frequency and plans for auditing trial conduct {23}

CCTU staff will review data entered on the database for errors and missing key data points. The trial database will also be programmed to generate reports on errors and error rates. Data quality issues will regularly be communicated to the TT. Essential trial issues, events and outputs, including defined key data points, will be detailed in the MICE trial Data Management Plan.

The frequency, type and intensity of routine and triggered on-site monitoring conducted by CCTU on behalf of the sponsor will be detailed in the MICE Quality Management and Monitoring Plan (QMMP). The QMMP will also detail the procedures for review and sign-off of monitoring reports.

### Plans for communicating important protocol amendments to relevant parties (e.g. trial participants, ethical committees) {25}

The CCTU ensure that the current trial protocol, patient information sheet, consent form, GP letter and submitted supporting documents have been approved by the REC and site R&D departments prior to use in patient recruitment. The protocol and all agreed substantial protocol amendments will be documented and submitted for ethical approval prior to implementation. Where changes are planned to patient-facing documentation, PPI groups will be consulted in advance for input.

## Dissemination plans {31a}

The dissemination plans follow best-practice recommendations. The plan is to engage with policy-makers, patients, carers, the public and media contacts to disseminate the findings across the public and private sectors and charities. We plan to publish the findings in peer-reviewed journals, and at national and international conferences. We will work with professional colleges, funders, the Epilepsy 12 national audit group and our PPI group to disseminate the findings widely to all stakeholders via traditional and social media.

## Response to COVID-19

The COVID-19 pandemic may have a significant impact on the mental health of participants. We therefore plan to ask a series of questions at 6 and 12 months post-randomisation to understand how participants and their families have been affected in order to help provide context to the findings of the study.

## Discussion

This protocol sets out the rationale and methods for evaluating the impact of adding a modular psychological intervention to usual care for young people with mental health disorders in the context of epilepsy. The psychological intervention will be delivered by non-mental health specialists from within epilepsy services in order to facilitate the closer integration of physical and mental health care. Given the high rates of mental health disorders coupled with high rates of unmet need in this group, positive results could result in suggestions for changes in service organisation and delivery in the UK and internationally. The model could also be used for the treatment of mental health disorders in children with other long-term conditions.

## Trial status

This manuscript presents the current version (4.0 of 27th July 2020) of the MICE Protocol. Recruitment commenced in May 2019. It was originally expected to be completed by May 2021 but due to delays resulting from the COVID-19 pandemic, is now anticipated to be completed by May 2022.

## Data Availability

Requests for access to trial data will be considered and approved in writing where appropriate, after formal application to the PSC. Considerations for approving access are documented in the PSC Terms of Reference (TOR).

## Abbreviations

AWS: Amazon Web Services
CA-SUS: Child and Adolescent Service Use Schedule
CAMHS: Child and Adolescent Mental Health Services
CBT: Cognitive behaviour therapy
CCTU: Comprehensive Clinical Trials Unit at UCL
CHU-9D: Child Health Utility 9-dimensions
CI: Chief Investigator
CIs: Confidence intervals
CNST: Clinical Negligent Scheme for Trusts
CTS-R: Cognitive Therapy Rating Scale Revised
CYP-IAPT: Children and Young People’s Improving Access to Psychological Therapies
DAWBA: Development and Well-being Assessment
DMEC: Data monitoring and ethics committee
DoH: Department of Health
DSM-5: Diagnostic and Statistical Manual of Mental Disorders
EQ-5D-5L: Five-dimension, five-level version of the EuroQol measure of health-related quality of life
ES: Effect size
GAD-7: Generalised Anxiety Disorder Assessment
GOSH: Great Ormond Street Hospital
GP: General Practitioner
HASS: Hague Seizure Severity Scale
ICC: Intraclass correlation coefficient
ICF: Informed consent form
ICH: Institute of Child Health
IQR: Interquartile range
ITT: Intention to treat
MATCH-ADTC: Modular Approach to Therapy for Children with Anxiety, Depression, Trauma or Conduct Problems
MICE: Mental Health Intervention for Children with Epilepsy
NHS: National Health Service
PASCET: Primary and Secondary Control Enhancement Training
PedsQL: Paediatric Quality of Life Epilepsy Module
PHQ-9: Patient Health Questionnaire
PIN: Participant identification number
PIS: Participant information sheet
PMG: Programme management group
PPI: Patient and public involvement
PSC: Programme steering committee
PSSRU: Personal Social Service Research Unit
QALY: Quality-adjusted life year
QMMP: Quality Management and Monitoring Plan
R&D: Research and development
RAG: Research advisory group
RCT: Randomised controlled trial
RCADS: Revised Child Anxiety and Depression Scale
REC: Research ethics committee
SAE: Serious adverse event
SAP: Statistical analysis plan
SDQ: Strengths and Difficulties Questionnaire
TT: Trial Team
ToR: Terms of Reference
UCL: University College London
VABS: Vineland Adaptive Behaviour Scales
